## I SYNOPSIS

|                                       |                                                                                                                                                                                                                                                                        |                                                                                                                                                                                         |
|---------------------------------------|------------------------------------------------------------------------------------------------------------------------------------------------------------------------------------------------------------------------------------------------------------------------|-----------------------------------------------------------------------------------------------------------------------------------------------------------------------------------------|
| Study Title                           | Supporting people with type 2 diabetes in effective use of their medicine through a system comprising mobile health technology integrated with clinical care compared with usual care: a randomised feasibility trial                                                  |                                                                                                                                                                                         |
| Internal ref. no. (or short title)    | SuMMiT-D Feasibility: SUpport through MObile MESSaging and digital health Technology for DIabetes / SuMMiT-D: Feasibility                                                                                                                                              |                                                                                                                                                                                         |
| Study Design                          | Multicentre randomised controlled feasibility trial                                                                                                                                                                                                                    |                                                                                                                                                                                         |
| Study Participants                    | Cohort 1 - Patients aged ≥35 years with type 2 diabetes
Cohort 2 – Primary care health professionals                                                                                                                                                                |                                                                                                                                                                                         |
| Planned Sample Size                   | Cohort 1 - We aim to recruit 200 patients
Cohort 2 - We aim to recruit between 12 and 30 healthcare professionals based on considerations of data saturation                                                                                                        |                                                                                                                                                                                         |
| Follow up duration                    | Two years                                                                                                                                                                                                                                                              |                                                                                                                                                                                         |
| Planned Study Period                  | 01/09/ 2018 to 31/08/ 2021                                                                                                                                                                                                                                             |                                                                                                                                                                                         |
| 
ObjectivesOutcome Measures
 |                                                                                                                                                                                                                                                                        |                                                                                                                                                                                         |
| Primary                               | To test participant recruitment to trial and willingness to be randomised.                                                                                                                                                                                             | To measure recruitment against planned recruitment rates.

Number of people showing an interest and not proceeding or those who withdraw from the control group and give a reason |
| Secondary                             | i. To assess the feasibility of collection of clinical measurement data for the proposed clinical trial. (With particular interest in prior to entry or following trial entry measurement collection of participant's HbA1c, systolic blood pressure and cholesterol). | i. Completeness of data collection of HbA1c, systolic blood pressure and total to HDL cholesterol ratio.                                                                                |
|                                       | ii. To test willingness of participants to be followed up over the 26-week period post randomisation.                                                                                                                                                                  | ii. Retention and follow-up rates.                                                                                                                                                      |
|                                       | iii. To test the collection of prescribing data on trial participants.                                                                                                                                                                                                 | iii. Proportion of medication possession ratio for glucose, blood pressure and lipid lowering medication obtainable.                                                                    |
|                                       | iv. To test the collection of self-reported questionnaire measures.                                                                                                                                                                                                    | iv. Proportions of completed self-reported measures.                                                                                                                                    |

|                     |                                                                                                                                                                                                                                                                                                                                                                                                                                   |                                                                                                                                                                                                                                                                                                                        |
|---------------------|-----------------------------------------------------------------------------------------------------------------------------------------------------------------------------------------------------------------------------------------------------------------------------------------------------------------------------------------------------------------------------------------------------------------------------------|------------------------------------------------------------------------------------------------------------------------------------------------------------------------------------------------------------------------------------------------------------------------------------------------------------------------|
|                     | 
v. To assess the feasibility and acceptability of the intervention for patients and healthcare professionals (including general practitioners, nurses, receptionists and pharmacists).
 
vi. To assess and understand the mechanisms of action of brief health related messages on self-reported adherence.
 
vii. To assess feasibility and acceptability of self-completion of the resource use questionnaire.
 | 
v. Data obtained through focus groups/qualitative interviews with patients and recruiting healthcare staff.
 
vi. Change in quantitative process measures and relationship between changes in these measures and self-reported adherence.
 
vii. Proportions of completed resource use questionnaire.
 |
| Exploratory  | 
viii. Changes in primary and secondary measures that will be used in the main trial
 
ix. Information on message delivery and interaction with participants.
                                                                                                                                                                                                                                                          | 
viii. Differences between time points obtained from baseline to six months.
 
ix. Automated reports from messaging service on messages delivered and interactive messaging
                                                                                                                                 |
| Intervention | Brief, tailored behaviour change messages delivered to people with type 2 diabetes focusing on use of medication using a mobile phone based system.                                                                                                                                                                                                                                                                               |                                                                                                                                                                                                                                                                                                                        |

## II ABBREVIATIONS

|        |                                                                  |
|--------|------------------------------------------------------------------|
| AE     | Adverse Event                                                    |
| AR     | Adverse Reaction                                                 |
| BCT    | Behaviour Change Technique                                       |
| CI     | Chief Investigator                                               |
| CRF    | Case Report Form                                                 |
| CTRG   | Clinical Trials and Research Governance                          |
| DMC    | Data Monitoring Committee / Data Monitoring and Safety Committee |
| GP     | General Practitioner                                             |
| GCP    | Good Clinical Practice                                           |
| HbA1c  | Glycated Haemoglobin                                             |
| HRA    | Health Research Authority                                        |
| ICH    | International Conference on Harmonisation                        |
| ICMJE  | International Committee of Medical Journal Editors               |
| ISRCTN | International Standard Randomised Controlled Trials Number       |
| MARS   | Medication Adherence Rating Scales                               |
| NHS    | National Health Service                                          |
| NIHR   | National Institute for Health Research                           |
| PC-CTU | Primary Care Clinical Trials Unit                                |
| PIL    | Participant Information Leaflet                                  |
| PSC    | Programme Steering Committee                                     |
| REC    | Research Ethics Committee                                        |
| SAE    | Serious Adverse Event                                            |
| SAR    | Serious Adverse Reaction                                         |
| SMS    | Short Message Service                                            |
| SOP    | Standard Operating Procedure                                     |
| SUSAR  | Suspected Unexpected Serious Adverse Reactions                   |
| TIA    | Transient Ischemic Attack                                        |
| TMG    | Trial Management Group                                           |

## **1 BACKGROUND AND RATIONALE**

### **1.1 Disease area**

Type 2 diabetes is a lifelong condition that causes a person's blood sugar to become too high. It can cause serious long-term health problems. 3.4 million people in the UK are affected . Treatments to reduce risks of complications from type 2 diabetes are effective if taken as intended. Concerns about medicines and difficulties in taking them regularly, whether intentional or unintentional, are common. Some services to help are available, but evidence of their effectiveness and cost-effectiveness is weak. These services may not be right for everyone and are not designed for repeated use. Not everyone has access to this extra help.

In addition to the burden of preventable death and disability, the cost of non-adherence with diabetes treatments has been estimated at £100 million per year in avoidable treatment costs.  Understanding and improving this situation could make a major contribution to health and NHS costs. At the moment managing the cost of diabetes complications takes up 10% of the NHS budget.

### **1.2 Evidence from systematic reviews**

Systematic reviews do not provide strong evidence to support the wider use of current approaches to developing interventions to support adherence.  Brief messages delivered at a wide-scale and low cost via digital health systems added to usual care have been shown to be effective in improving health for some conditions and are a promising approach to the problem. 

Systematic reviews of text-messaging to support adherence to treatment and mobile health interventions in diabetes identify some effective interventions. There are a few trials testing the impact of brief messaging in type 2 diabetes, but they do not have systematically developed interventions and are at risk of bias.  Recent trials of Short Message Service (SMS) text-messaging for cardiovascular risk prevention and blood pressure lowering have shown clinically relevant changes in outcomes compared with usual care. 

Systematic reviews offer substantial evidence that tailored interventions are more effective than generic interventions. Tailored interventions may be seen by recipients as more personally relevant, so they will be more likely to attend to, read, understand, and act on them. In addition, tailored interventions are designed to change determinants of the target behaviour that are relevant to particular individuals (or to small subgroups of individuals); they therefore more precisely target the determinants of the individual's behaviour. There is scope for developing more highly tailored interventions for medication adherence using interactive voice response, SMS, and other digital platforms, although the potential benefit of increased effectiveness has to be balanced against the increased burden of measurement and greater complexity.

### **1.3 Preliminary data**

In the formative work for this trial, we have examined which types of messages are most useful for people starting and taking a diabetes medicine and examined the extent to which messages can be tailored to the individual using routinely available NHS data. We have also explored the extent to which it is valuable for patients to decide on the types of messages to which they want to receive and respond.

### **1.4 Aims of current study**

This trial is intended to inform the feasibility and design of a future clinical trial to estimate the extent of benefit and costs of a brief-messaging mobile based intervention compared to usual care in patients with type 2 diabetes as they start new medication and identify difficulties that might be encountered in practice. This research could offer a model for technology-based self-management support that could be extended to other aspects of diabetes care and other long-term conditions.

## 2 OBJECTIVES, STUDY PARAMETERS AND ENDPOINTS

### 2.1 Summary of objectives and outcomes

| Objectives                                                                                                                                                                                                                                                                                      | Outcome Measures                                                                                                                                                              | Time-point(s) of evaluation of this outcome measure                                                 |
|-------------------------------------------------------------------------------------------------------------------------------------------------------------------------------------------------------------------------------------------------------------------------------------------------|-------------------------------------------------------------------------------------------------------------------------------------------------------------------------------|-----------------------------------------------------------------------------------------------------|
| To test participant recruitment to trial and willingness to be randomised.                                                                                                                                                                                                                      | Recruitment against planned recruitment rates.

Number of people showing an interest and not proceeding or those who withdraw from the control group and give a reason. | End of recruitment period.                                                                          |
| i. To assess the feasibility of collection of clinical measurement data for the proposed 15-month clinical trial. (With particular interest in 15 months prior to trial entry or following trial entry measurement collection of participant's HbA1c, systolic blood pressure and cholesterol). | i. Completeness of data collection of HbA1c, systolic blood pressure and total to HDL cholesterol ratio.                                                                      | i. End of follow-up period.                                                                         |
| ii. To test willingness of participants to be followed up over the 26-week period post randomisation.                                                                                                                                                                                           | ii. Retention and follow-up rates.                                                                                                                                            | ii. End of follow-up period.                                                                        |
| iii. To test the collection of prescribing data on trial participants.                                                                                                                                                                                                                          | iii. Proportion of medication possession ratio for glucose, blood pressure and lipid lowering medication obtainable.                                                          | iii. End of follow-up period.                                                                       |
| iv. To test the collection of self-reported questionnaire data.                                                                                                                                                                                                                                 | iv. Proportion of completed self-reported measures.                                                                                                                           | iv. End of follow-up period.                                                                        |
| v. To assess the feasibility and acceptability of the intervention for patients and healthcare professionals (including general practitioners,                                                                                                                                                  | v. Data obtained through focus groups/qualitative interviews with patients and recruiting healthcare staff.                                                                   | v. Baseline and end of follow-up for patients and throughout the trial period for healthcare staff. |

|                                                                                                                   |                                                                                                                             |                                                                                                       |
|-------------------------------------------------------------------------------------------------------------------|-----------------------------------------------------------------------------------------------------------------------------|-------------------------------------------------------------------------------------------------------|
| nurses, receptionists and pharmacists).                                                                           |                                                                                                                             |                                                                                                       |
| vi. To assess and understand the mechanisms of action of brief health related messages on self-reported adherence | vi. Change in quantitative process measures and relationship between changes in these measures and self-reported adherence. | vi. End of follow up period qualitative interviews/survey/telephone contacts with trial participants. |
| viii. To assess feasibility and acceptability of self-completion of the resource use questionnaire.               | vii. Proportion of completed resource use questionnaire.                                                                    | vii. End of follow-up period.                                                                         |
| Exploratory measures                                                                                              | viii. Changes in primary and secondary measures that will be used in the main trial.                                        | viii. Differences between time points obtained from baseline to 26 weeks.                             |
|                                                                                                                   | ix. Information on message delivery and interaction with participants.                                                      | ix. Automated reports from messaging service on messages delivered and interactive messaging          |

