### 2.2.2 Secondary outcomes

Secondary outcomes focus on feasibility of collection of clinical measurement data for the proposed main trial (where 15-month follow up is planned to ensure collection of clinical data collected annually). Of main interest is the feasibility of obtaining two measurements from the medical records, of HbA1c, systolic blood pressure and cholesterol from trial participants in a 15-month period, either prior to an entry measurement, or following trial entry. We will do this by collecting historical data to check frequency of HbA1c measurement in the prospective trial population.

Additional secondary outcomes are to measure follow-up of participants over a 26-week period and to test the collection of prescribing data on trial participants. We will obtain prescribing records for trial participants and report the proportion in which there is sufficient data to estimate availability of blood glucose, blood pressure and cholesterol lowering medications as a proportion of that expected. We will also measure the proportion of self-reported measures collected as the proportion of EQ-5D-5L. Potential mechanisms for the action of the brief messages will be assessed through changes in hypothesised health psychology constructs relating to use of medication, self-report medication adherence, and questions based on the Technology Acceptance model. We will collect resource use data.

We will use qualitative methods to assess the feasibility and acceptability of the intervention for patients and also among health care workers (including general practitioners, nurses, receptionists and pharmacists).

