##### 3.1.1 Process evaluation (Cohort 1 - trial participants)

The process evaluation will consider mechanism, context and implementation using both quantitative and qualitative methods. The purpose of the evaluation will be to decide if any of the messages, or behaviour change techniques should be omitted prior to the main trial. Participants will be purposefully selected from the feasibility trial and invited to take part in qualitative interviews and post-follow up debriefing phone calls to share their views on the messaging system, insight into how it was implemented in daily life, identify issues around potential attrition and inform final procedures for the main trial (see *Section 4.1 Qualitative work with study participants* for further information). Up to 30 patients will be recruited.

If there is no change in the quantitative measure of proposed mechanisms, and there is qualitative evidence that certain behaviour change techniques (BCTs) and/or messages are disliked by participants, or have a negative impact on implementation these will be omitted prior to the main trial.

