## 6 STATISTICS

### 6.1 Description of Statistical Methods

The analysis will be carried out once the final patient has completed their 26-week follow up. An intention to treat approach will be used, where all participants randomised will be included in the group to which they were allocated, regardless of intervention received. The results of the primary and secondary objectives will be presented descriptively using proportions and 95% confidence intervals.

The primary outcome will be the number of patients recruited and randomised as a proportion (with 95% confidence interval) of the target recruitment number.

Secondary outcomes, including loss to follow up (%), withdrawals (%) and completeness of data collection for various outcomes (%), will be presented overall and separately by treatment group.

Exploratory outcomes (changes in primary and secondary measures to be used in the main trial) will be analysed using an intention to treat approach. Continuous outcomes will be analysed using an analysis of covariance adjusting for minimisation factors. Results will be presented as a difference in means with 95% confidence interval. Binary outcomes will be analysed in a similar way using log binomial regression models (adjusting for minimisation factors). Results will be presented as relative risks with 95% confidence intervals.

A detailed statistical analysis plan will be prepared prior to data lock.

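### Objective vi asks how the messages act on adherence, but its outcome states no comparison between randomised arms, so it cannot by itself show mechanism

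*Protocol*

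**What the plan says.** The objective, in the synopsis and in Protocol section 2.1, is causal: "To assess and understand the mechanisms of action of brief health related messages on self-reported adherence". The outcome set against it is "Change in quantitative process measures and relationship between changes in these measures and self-reported adherence". It has two parts: change in the process measures, and how those changes relate to adherence. Section 2.2.2 repeats the first part: "Potential mechanisms for the action of the brief messages will be assessed through changes in hypothesised health psychology constructs". None of these places names a comparison of the two arms.

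On analysis, section 6.1 says: "The results of the primary and secondary objectives will be presented descriptively using proportions and 95% confidence intervals". It then says that secondary outcomes, with loss to follow-up, withdrawals and data completeness as its examples, "will be presented overall and separately by treatment group". A between-arm model comes only in the next paragraph, for exploratory outcomes: "Continuous outcomes will be analysed using an analysis of covariance adjusting for minimisation factors", reported as a difference in means with a 95% confidence interval. Exploratory outcomes are the measures intended for the main trial. The protocol does not list them, so MARS may be among them; the process constructs are not said to be.

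Sections 3.8.1 and 3.8.2 and Appendix B show that participants in both arms complete MARS and the health psychology questionnaire at baseline and at 26 weeks.

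**The concern.** A construct is a mechanism of the messages only if the messages move it. The randomised comparison of that construct is the direct evidence, and the outcome for objective vi does not ask for it.

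The two things it does ask for can both arise without any message effect. Under section 3.4.1.1 every participant has started or changed a relevant medicine within the last three months, so beliefs and habits may shift over 26 weeks in either arm. The constructs and MARS are self-reported at the same two times, so their changes may be correlated in either arm for reasons unrelated to the messages.

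At stake is what the trial can say about its own objective. A construct could be reported as a route by which the messages work because it tracks adherence, although the messages did not change it. Process data also feed a decision on content: the rule in section 3.1.1 begins "If there is no change in the quantitative measure of proposed mechanisms, and there is qualitative evidence that certain behaviour change techniques", and there too the change is not tied to arm.

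**Working it through.** **Inputs**

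- 200 participants, 100 per arm (section 6.2).
- 80% follow-up, the planning value in section 6.2: 0.80 × 200 = 160 completers, 80 per arm.
- Two-sided 5% test. This is an assumption, taken from the 95% intervals in section 6.1; no test is stated for objective vi.
- Correlation r between change in a construct and change in adherence when the messages do nothing. The protocol gives no value, so a range is shown.

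**The plan's own figure.** The exact (Clopper-Pearson) 95% interval for 160/200 is 73.78% to 85.31%, which agrees with the 73.8% to 85.3% in section 6.2. It concerns follow-up; no sample-size figure is given for objective vi.

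**Step 1: the association when the messages do nothing.** By Fisher's z, the probability of a significant correlation is approximately Φ(atanh(r)·√(n−3) − 1.96), plus a negligible opposite tail for r of 0.1 or more. With n = 160, √157 = 12.53:

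- r = 0.1: 0.1003 × 12.53 = 1.257; Φ(−0.703) ≈ 0.24
- r = 0.2: 0.2027 × 12.53 = 2.540; Φ(0.580) ≈ 0.72
- r = 0.3: 0.3095 × 12.53 = 3.878; Φ(1.918) ≈ 0.97

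Simulation with no arm effect on either score (10,000 trials, 80 per arm) agrees. The last two columns come from the same runs.

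| Assumed r | Pooled association, n = 160 | Association adjusted for arm, n = 160 | Intervention arm only, n = 80 | Arm difference in construct | Arm difference and adjusted association both significant |
|---|---|---|---|---|---|
| 0 | 4.9% | 4.8% | 4.9% | 5.1% | 0.2% |
| 0.1 | 24.1% | 23.9% | 14.6% | 5.0% | 1.2% |
| 0.2 | 71.9% | 71.6% | 43.4% | 5.1% | 3.5% |
| 0.3 | 97.1% | 96.9% | 78.0% | 4.6% | 4.4% |
| 0.4 | >99.9% | >99.9% | 96.1% | 4.8% | 4.8% |

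**Step 2: where the protection lies.** Adding arm to the association model leaves its positive rate unchanged (second and third columns). The randomised comparison of the construct stays near 5% whatever r is. What is missing is that comparison, not a covariate in the association.

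**Step 3: precision of the comparison.** For an unadjusted difference with 80 per arm, the 95% half-width is 1.96 × √(1/80 + 1/80) = 1.96 × 0.158 = 0.31 SD.

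**The case against.** The strongest reply is that the protocol is being held to a standard it does not claim. Section 6.1 presents secondary objectives descriptively. No test, threshold or success criterion attaches to objective vi, and nothing says that a significant correlation makes a construct a mechanism. The outcome also includes change in the process measures, and section 6.1 says that secondary outcomes are shown by treatment group. Section 2.1 evaluates the objective partly through interviews, surveys and telephone contacts. A detailed SAP is promised, and a mediation model belongs there.

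Much of this stands. The 5% rule in the working is an assumption, and the mediation model is a SAP matter. Display by arm may well extend to objective vi, although the examples given are feasibility rates.

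It does not remove the point. Display by arm is not a between-arm estimate with an interval. The change in the first half of the outcome is not tied to arm. Interviews are with the intervention group only (section 4.1), so they supply no contrast. The mismatch lies in the protocol's own outcome definition and reporting format: a format that "will be presented descriptively using proportions and 95% confidence intervals" does not suit a change score or an association.

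Three stronger readings are tempting and are not supported:

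- **That the analysis will nearly always look positive.** A rate of 95% needs r of about 0.28 at n = 160, or 0.39 in one arm of 80. The protocol gives no r.
- **That the control arm goes unused.** The display by treatment group may cover this outcome.
- **That the correlation decides which messages go forward.** The omission rule in section 3.1.1 uses change in the process measure together with qualitative evidence; the association is not an input.

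**Conclusion.** The point holds in a limited form. Objective vi is about the effect of the messages, while its stated outcome contains no randomised comparison, and section 6.1 assigns it a format that does not fit. As written, the measure cannot separate a message effect from change and co-movement that would occur in both arms.

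The size depends on a correlation that the documents do not give. With no message effect, 160 completers and an assumed two-sided 5% test, the association would be significant in about 24%, 72% and 97% of trials at r = 0.1, 0.2 and 0.3. Against this, a between-arm comparison of the construct would be positive in about 5%. These figures also assume that all 160 have both scores at both times.

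The primary outcome, recruitment, is unaffected. The change is worth making because the trial already collects what is needed to address the objective properly.

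**What to change.** In the synopsis and section 2.1, reword outcome vi so that each process measure and MARS at 26 weeks is compared between randomised arms. In section 6.1, add that this uses the analysis of covariance already planned, adjusted for the minimisation factors and the baseline score of the same measure, and is reported as a difference in means with a 95% confidence interval.

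State in the same place that the association between construct and adherence is descriptive and supportive only, and that a construct is described as a candidate mechanism only where the between-arm difference supports it. Any mediation or indirect-effect model can be left to the SAP.

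The cost is a few sentences and a few extra models on data already collected in both arms. The downsides are wide intervals (about ±0.31 SD unadjusted at 160 completers) and probably fewer constructs that look positive. The step from construct to adherence remains observational.
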